### 2.8. Termination of Participation

Participation in this registry may terminate early for reasons such as withdrawal of informed consent, the patient being found to be ineligible, investigator’s discretion (e.g., patient noncompliance), no osseous reconstruction with autologous bone performed within 18 months from resection, loss to follow-up, death, sponsor’s decision, or other reasons. Early terminations will be recorded in a dropout form, including the circumstances leading to the termination. All patient data collected before termination will be censored as of the day of the official withdrawal. Censored data will be included in the analysis, unless a patient explicitly requested removal of their data.

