Generally, all eligible patients who commenced treatment within the registry (i.e., having mandibular resection ≥2 cm and receiving reconstruction within 18 months after mandibular resection) will be included in the analysis. If a patient drops out, data collected up until that point will be included in the analysis. For specific research questions, only certain subgroups of patients may be relevant, and this will be predefined before the analysis. Depending on the amount and quality of the collected data, further appropriate statistics will be applied. Information on the analysis populations, the criteria for inclusion, the handling of missing data, and protocol violations will be defined and specified in the SAP.

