One strength of this registry study is that it will capture the resources invested to rehabilitate the addressed group of patients, with the registry-based approach allowing for the collection of real-world longitudinal data across diverse clinical settings, enhancing external validity and enabling the evaluation of outcomes in routine practice. By using best practice for each of the treatment arms instead of randomisation, the clinical pathway of each contributing medical centre is not affected; however, the non-randomised design means the study may be subject to unmeasured confounding factors, such as comorbidities and socioeconomic status. Moreover, bias may be introduced through differences in surgeon experience, case selection, and institutional resources, despite adherence to each centre’s standard of care. In the addressed patient population, implant-borne dental rehabilitation could or should have been achieved—but often has not been—to date. For these patients, those who received bony reconstruction after 18 months (potentially due to individual health issues, which restrict them from undergoing bony reconstruction) will not be included. The outcomes of this registry may provide important insights into dental rehabilitation in the different patient populations, and perhaps some of the reasons for these diverse barriers to dental rehabilitation may be examined. The multicentre aspect of the registry will provide a wide range of evidence across different healthcare landscapes.

The extensive scope of this multicentre registry will create a knowledge database enabling the development of research hypotheses and future research to provide evidence that may help address some of these open questions.

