## Figures and Tables

**Figure 1 cmtr-19-00017-f001:**
[figure not shown]
Planned patient flow.

**Table 1 cmtr-19-00017-t001:** Current participating sites.

Name	Country
Uniklinik RWTH Aachen, Aachen	Germany
Charité—Universitätsmedizin Berlin, Corporate Member of Freie Universität Berlin and Humboldt-Universität zu Berlin, Department of Oral and Maxillofacial Surgery, Berlin	Germany
Hannover Medical School	Germany
University Hospital Heidelberg	Germany
University Hospital Leipzig	Germany
LMU University Hospital, Munich	Germany
University Hospital Tübingen	Germany
Military Hospital Ulm	Germany
Shimane University Hospital, Izumo	Japan
Erasmus University Medical Centre, Rotterdam	The Netherlands
Instituto Português de Oncologia de Lisboa, Lisbon	Portugal
12 de Octubre University Hospital, Madrid	Spain
Uppsala University Hospital, Uppsala	Sweden
University Hospital Basel, Basel	Switzerland
University of Illinois Hospital (UIHealth), Chicago	USA
Tarrant County Hospital, Fort Worth	USA
University of Florida College of Medicine, Jacksonville	USA
Mount Sinai Hospital, New York	USA

**Table 2 cmtr-19-00017-t002:** Inclusion and exclusion criteria.

Inclusion Criteria	Preoperative Exclusion Criteria	Additional Exclusion Criteria
- Age 18 years and older - Patients undergoing reconstruction of mandibular defects of ≥2 cm in size following segmental resection of pathologic mandibles due to oral tumours (including OSCC, osteosarcoma, and ameloblastoma), medication-related osteonecrosis of the jaw associated with bisphosphonates or immunomodulatory agents, or metastatic disease from primary sites, such as the lung, breast, prostate, liver or kidney - Intention to undergo mandibular reconstruction with autologous bone using a primary (one-stage) or secondary (two-stage) approach - Informed consent obtained according to IRB/EC procedures	- Tumours affecting the condyle - Patients under palliative care - Previous extensive mandibular surgeries (including reconstructions, e.g., TMJ replacement) that may potentially confound the outcome measures	- No osseous reconstruction with autologous bone performed within 18 months of resection

EC, ethics committee; IRB, investigational review board; OSCC, oral squamous cell carcinoma; TMJ, temporomandibular joint.

**Table 3 cmtr-19-00017-t003:** Data collection at each visit.

Assessment Parameters	Pre-, Intra-, and Postoperative Visits *									

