**Patient-reported outcomes**										
**OHIP**	X		X	X	X	X	X	X		X
**EQ-5D-5L**	X		X	X	X	X	X	X		X
**Patient satisfaction**					X	X	X	X		X
**Adverse events**		X	X	X	X	X	X	X	X	X
**Radiological assessment ^5^**	X	X	X	X	X	X	X	X	X	X

* Postoperative FU visits with the defined time windows are calculated from the day of mandibular resection (i.e., day 0) and reconstruction (if the patient undergoes primary reconstruction).^1^ Post-second-stage reconstruction visits will be calculated from the day of secondary reconstruction (day 0). Patients will be followed up for a maximum of 2 years from the time of mandibular resection. ^2^ Information on adjuvant treatment for the malignant conditions may be available at a different timepoint and will be documented whenever it becomes available. ^3^ Osseous reconstruction can occur on the day of resection (one-stage reconstruction) or on a different day (two-stage reconstruction). ^4^ Additional surgeries may occur at any time after mandibular resection. ^5^ All images will be taken according to the local standard of care and will be collected. Assessments will be performed on available images.

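### Restricting analysis to patients reconstructed within 18 months, while day 0 is resection, biases overall survival by staging, leaves failed pathways out, and conflicts with section 2.8

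*Protocol article*

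**What the plan says.** The entry criterion in Table 2 of the protocol article is prospective: "Intention to undergo mandibular reconstruction with autologous bone using a primary (one-stage) or secondary (two-stage) approach". A patient can therefore be enrolled and never reach reconstruction.

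Three places then remove such patients:
- Section 2.11 defines the general analysis set as eligible patients who commenced treatment, which it explains as "having mandibular resection ≥2 cm and receiving reconstruction within 18 months after mandibular resection".
- Table 2 lists as an additional exclusion "No osseous reconstruction with autologous bone performed within 18 months of resection".
- The Discussion says that "those who received bony reconstruction after 18 months" are left out, and names individual health issues as a possible cause.

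On timing, the footnote to Table 3 says "Postoperative FU visits with the defined time windows are calculated from the day of mandibular resection" and caps follow-up at 2 years from resection. Footnote 1 restarts a second series of visits at the secondary reconstruction. Survival is ticked in Table 3 from Visit 2 (day 0). Section 2.9.1 lists overall and recurrence-free survival without a time origin.

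Section 2.8 points the other way. It lists absence of autologous reconstruction within 18 months, and also death, among the reasons for early termination. It then says: "Censored data will be included in the analysis, unless a patient explicitly requested removal of their data".

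Section 2.11 plans summaries by treatment pattern. Section 2.2 includes outcomes by treatment modality (objective 2) and predictors of successful autologous reconstruction (objective 3).

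**The concern.** Membership of the analysis set depends on something that happens after day 0, and the delay before it can happen differs between the groups to be described. A two-stage patient in the set cannot have died before the second operation; a one-stage patient has no such protected period. This is immortal time, and it acts directly on overall survival from resection.

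Patients whose pathway failed before reconstruction are also missing from the other outcomes. The Introduction says it is unclear whether one-stage or two-stage surgery gives better results, and the Discussion wants to learn how far the goal of reconstruction is achieved and what stands in the way of dental rehabilitation. A set that starts from those who reached reconstruction cannot show how many did not, or why.

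The conflict with section 2.8 leaves it open whether these patients are in or out. Section 2.8 also lets their participation end, so later survival and adverse event data may not be collected.

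**Working it through.** **No plan figure to reproduce.** The article gives no power, precision, survival or delay figure, and the 300 patients are a feasibility number. What follows illustrates size under stated assumptions.

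**Inputs from the article.** Day 0 is resection; the latest qualifying reconstruction is at 18 months; maximum follow-up is 24 months from resection. The protected period for death is thus 0 for one-stage patients and at most 18/24 = 75% of follow-up for two-stage patients.

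**Assumed inputs.** True 24-month survival S is the same in both groups, the hazard is constant, and every second stage takes place at the same delay of d months.

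**Formulas.** Apparent two-stage survival, given survival to the second operation, is S(24)/S(d) = S^(1 − d/24). The share of intended two-stage patients lost from the set by death alone is 1 − S^(d/24). The true difference between the groups is 0.

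Apparent two-stage 24-month survival, with the spurious gain in percentage points:

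| True S | d = 6 | d = 12 | d = 18 |
|---|---|---|---|
| 50% | 59.5% (+9.5) | 70.7% (+20.7) | 84.1% (+34.1) |
| 65% | 72.4% (+7.4) | 80.6% (+15.6) | 89.8% (+24.8) |
| 80% | 84.6% (+4.6) | 89.4% (+9.4) | 94.6% (+14.6) |
| 90% | 92.4% (+2.4) | 94.9% (+4.9) | 97.4% (+7.4) |

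For example, with S = 65% and d = 12, 0.65^(1 − 12/24) = 0.65^0.5 = 0.806. The share lost by death alone at S = 65% is 1 − 0.65^0.25 = 10.2%, 1 − 0.65^0.5 = 19.4% or 1 − 0.65^0.75 = 27.6% for d = 6, 12 or 18.

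The direction does not need the constant hazard: S(24)/S(d) exceeds S(24) whenever any deaths occur before d.

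**Other outcomes.** Section 2.10 starts adverse event collection at enrolment, and Table 3 records adverse events from Visit 2. A recurrence, plate problem or other event during the wait therefore counts if the patient is later reconstructed in time. What is missing is the experience of those never reconstructed in time. The article gives nothing from which to size that loss or to sign its effect.

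**Numbers so far.** Section 2.13 reports 138 enrolled and 118 meeting eligibility, a gap of 20 (20/138 = 14.5%). Reasons are not given.

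**The conflict.** Take a two-stage patient who dies at month 10 without reconstruction. Under section 2.8 this is an early termination whose data are analysed. Under section 2.11 the patient never met the condition for the analysis set. A patient alive at 18 months without reconstruction is likewise in under section 2.8, and out under section 2.11 and Table 2.

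**The case against.** The registry is exploratory, with descriptive statistics, no primary outcome and no planned test of staging. Section 2.11 says its rule applies generally, allows predefined subgroups and leaves details of the populations to the SAP. Predictors of graft success among reconstructed patients are a legitimate target, and for that question a reconstructed-only set is right. Footnote 1 to Table 3 already restarts visits at the second operation, and the Discussion discloses the restriction.

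Much of this stands. It limits the harm to biased description rather than a false test result, and it supports keeping the reconstructed-only set for graft and implant outcomes. It does not remove the problem: the inclusion rule is already stated and is also an exclusion criterion, and a SAP cannot restore follow-up that ended under section 2.8.

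Three stronger readings are tempting and are not supported:
- A reader might infer that every outcome will favour two-stage surgery by construction. Only death is excluded during the wait. Two-stage patients also have two operations at which adverse events can arise, so the direction for adverse events could reverse.
- A reader might infer that patients who recur or lose the bridging plate while waiting are removed. They are removed only if they are not reconstructed within 18 months.
- A reader might take the 20 of 138 as the number lost this way. The article does not say so.

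**Conclusion.** The analysis set in section 2.11 conditions on a post-baseline event while day 0 and the follow-up cap are set at resection. If survival is timed from resection, overall survival by treatment pattern is biased towards two-stage surgery. That origin is inferred from the visit schedule and should be stated. For recurrence, adverse events and dental rehabilitation the finding is selection of unknown size and direction.

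The spurious survival gain is about 5 to 34 points for true 24-month survival of 80% to 50%, and as little as 2.4 points at 90%, which matters in a cohort that includes ameloblastoma and drug-induced osteonecrosis. The largest values need every second stage at the 18-month limit. All rest on assumed survival and delays, so they show what could happen, not what will.

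If section 2.8 governs, these patients are not dropped from the analysis, although their follow-up may still end early. The contradiction between section 2.8 and section 2.11, Table 2 and the Discussion is certain on the text and has to be resolved.

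**What to change.** 1. Reconcile section 2.8 with section 2.11, Table 2 and the Discussion, so that it is clear whether patients without timely reconstruction are analysed. State the time origin for survival.
2. For survival, adverse events and the share reaching reconstruction, analyse all patients who met the preoperative criteria and had a resection of at least 2 cm, grouped by the one- or two-stage strategy intended.
3. Report autologous reconstruction by 18 months as an outcome, with death as a competing event and with the reasons for non-performance that section 2.5.2 already collects.
4. For any survival contrast by treatment actually received, use a landmark or treat reconstruction as a time-dependent exposure.
5. Time graft and implant outcomes from reconstruction, and keep the reconstructed-only set for these and as a secondary set. Under the cap, only 24 − 18 = 6 months remain after a second stage at 18 months, so time at risk should be shown.
6. Where feasible, continue collecting standard-of-care survival and adverse event data to 24 months for patients not reconstructed.

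Items 2 to 5 are mainly SAP wording and use data that are largely recorded already. Items 1 and 6 need a protocol amendment, and item 6 adds data collection in a group of unknown size. Success rates will look somewhat less favourable once failures are in the denominator. The work should be done before the analysis planned for May–September 2026.

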### 2.12. Termination Criteria

The progress of the registry will be closely monitored, in particular the enrolment and safety aspects. Though there are no a priori termination criteria, the registry may be stopped for varying reasons (e.g., the registry fulfilling its purpose, poor quality of data, the registry being no longer relevant, and loss of funding/support to carry out the registry).

### 2.13. Current Status

The protocol in operation is version 3.0, dated 12 December 2024, as reflected in the manuscript, with protocol changes (inclusion and exclusion criteria) from the previous version. There are 13 participating sites from Europe, one from Japan, and four from North America, with ethics approval obtained from all sites. Sixteen sites have enrolled 138 patients, of whom 118 have thus far met the eligibility criteria. The first patient was enrolled in November 2022, and the data analysis is planned for May–September 2026.

### 2.14. Ethics and Dissemination

Data from each patient participating in the registry are documented in electronic case report forms (CRFs) and captured in the REDCap Cloud Electronic Data Capture system (http://www.redcapcloud.com) [27,28]. CRFs should be completed in a timely manner after the patient’s visit and are password-protected, with only authorised personnel having access. After termination of the registry, each site will receive an electronic copy of the data collected from the respective registry site. Because this study is observational, only standard-of-care procedures are performed, and only anticipated condition-related AEs are collected. Therefore, a data safety monitoring board has not been implemented. Data monitoring and cleaning will be performed on a regular basis to ensure data accuracy.

Ethics approval from the local ethics committee or institutional review board was obtained for each site before enrolling patients. The registry was designed and will be carried out according to current valid international guidelines (International Council for Harmonisation of Technical Requirements for Pharmaceuticals for Human Use (ICH) Guideline for Good Clinical Practice E6 [29] and ISO 14155 [30]), with the ethical position based on the Declaration of Helsinki, thus ensuring optimal protection of patient interests. The results of this study are intended to be published in peer-reviewed journals.

## 3. Discussion

This study protocol describes an international registry that will provide standardised information to support future clinical research and generate medical and clinical evidence on reconstruction following segmental mandibular resection for diverse pathologies, thereby assisting clinical decision-making. The study protocol was amended to widen the inclusion criteria to capture a larger number of patients with pathologies other than OSCC that necessitate reconstruction after segmental mandibular resection. This reflects the recent increase in defect reconstruction seen for non-primary cancer lesions in the mandible. Primary cancers such as lung, breast, prostate, or kidney cancers commonly metastasise to the mandible [31]. The positive outcome of increased survival of patients with such cancers due to advanced cancer treatments is countered by a potentially increased risk of developing metastases in the mandible. This, coupled with the complexity of different treatment options and constant technological innovation, has created a landscape in which it is difficult to obtain satisfactory evidence on the effectiveness of each treatment combination.

Many clinical questions remain in the present clinical landscape. These include the known limitations of donor sites; specifically, it is unclear how donor site morbidity influences the prolonged rehabilitation of patients undergoing reconstruction following segmental mandibular resection. Further, it is unclear whether the QoL of patients undergoing two-stage reconstruction is improved if a longer rehabilitation process is avoided. The primary endpoint of a reconstruction should be the ability to offer all patients a dental rehabilitation protocol, yet in the present treatment environment, only 15–20% of SMDR patients receive dental implants [8,9,10,11,12]. Moreover, mandibular reconstruction following tumour/mandibular resection poses notable challenges for treatment outcomes, particularly due to limitations inherent in both one-stage and two-stage osseous reconstruction techniques. One-stage reconstruction enables faster restoration but may result in suboptimal outcomes due to intraoperative difficulties in accurately contouring the graft, especially in complex defects, leading to impaired dental rehabilitation, aesthetic compromise, and increased flap failure risk. Two-stage reconstruction facilitates more effective treatment planning for complex defects and allows a period of bone adaptation before the final reconstruction but delays rehabilitation, increases infection and scarring risks, and often requires multiple interventions, adversely affecting recovery and overall clinical outcomes. Another aspect of this study will be to investigate the extent to which the principal goal of mandibular bone reconstruction can be realised and the cumulative surgical, prosthodontic, and logistical demands involved before achieving functional or even theoretically viable dental rehabilitation. This study has a two-year follow-up period; although it may not be sufficient to evaluate long-term outcomes, it will allow assessment of whether the reconstruction can be used for a dental implant and dental rehabilitation protocol. Any such dental rehabilitation should ideally take place within a time period of up to two years after the segmental defect reconstruction.

The amendment to the protocol, which involved broadening the inclusion criteria, has improved the recruitment rate. However, achieving the planned sample size still needs considerable time and represents a key limitation of the study. Additionally, the inclusion of a wider range of mandibular pathologies, such as osteosarcoma, ameloblastoma, oral metastases, and drug-induced osteonecrosis beyond the initially targeted OSCC, introduces heterogeneity that may complicate data analysis and interpretation, which can be considered a further limitation of the current protocol. On the other hand, the assumed large sample size enhances the statistical power of the study and increases the reliability and generalisability of the findings. Moreover, the inclusion of a diverse range of mandibular pathologies in addition to OSCC allows for a more comprehensive evaluation of the reconstructive protocol across different clinical scenarios. This heterogeneity may provide valuable insights into the protocol’s applicability and effectiveness in managing a broader spectrum of mandibular defects, thereby improving its clinical relevance and translational potential.

One strength of this registry study is that it will capture the resources invested to rehabilitate the addressed group of patients, with the registry-based approach allowing for the collection of real-world longitudinal data across diverse clinical settings, enhancing external validity and enabling the evaluation of outcomes in routine practice. By using best practice for each of the treatment arms instead of randomisation, the clinical pathway of each contributing medical centre is not affected; however, the non-randomised design means the study may be subject to unmeasured confounding factors, such as comorbidities and socioeconomic status. Moreover, bias may be introduced through differences in surgeon experience, case selection, and institutional resources, despite adherence to each centre’s standard of care. In the addressed patient population, implant-borne dental rehabilitation could or should have been achieved—but often has not been—to date. For these patients, those who received bony reconstruction after 18 months (potentially due to individual health issues, which restrict them from undergoing bony reconstruction) will not be included. The outcomes of this registry may provide important insights into dental rehabilitation in the different patient populations, and perhaps some of the reasons for these diverse barriers to dental rehabilitation may be examined. The multicentre aspect of the registry will provide a wide range of evidence across different healthcare landscapes.

The extensive scope of this multicentre registry will create a knowledge database enabling the development of research hypotheses and future research to provide evidence that may help address some of these open questions.

